## Abstract

**Background:**

Inguinal hernia repair is one of the most common surgical procedures worldwide. This procedure is increasingly performed with endoscopic techniques (laparoscopy). Many surgeons prefer to cover the hernia gap with a mesh to prevent recurrence. The mesh must be fixed tightly, but without tension. During laparoscopic surgery, the mesh is generally fixed with staples or tissue glue. However, staples often cause pain at the staple sites, and they can cause scarring of the abdominal wall, which can lead to chronic pain. We designed a trial that aims to determine whether mesh fixation with glue might cause less postoperative pain than fixation with staples during a transabdominal preperitoneal patch plastic repair.

**Methods/Design:**

The TISTA trial is a prospective, randomized, controlled, single-center trial with a two-by-two parallel design. All patients and outcome-assessors will be blinded to treatment allocations. For eligibility, patients must be male, ≥18 years old, and scheduled for laparoscopic repair of a primary inguinal hernia. One group comprises patients with a unilateral inguinal hernia that will be randomized to receive mesh fixation with either tissue glue or staples. The second group comprises patients with bilateral inguinal hernias. They will be randomized to receive mesh fixation with tissue glue either on the right or the left side and with staples on the other side. The primary endpoint will be pain under physical stress, measured at 24 h after surgery. Pain will be rated by the patient based on a numeric rating scale from 0 to 10, where 10 equals the worst pain imaginable. A total of 82 patients will be recruited (58 patients with unilateral inguinal hernias and 24 patients with bilateral hernias). This number is estimated to provide 90% power for detecting a pain reduction of one point on a numeric rating scale, with a standard deviation of one.

**Discussion:**

Patients with bilateral hernias will receive two meshes, one fixed with glue, and the other fixed with staples. This design will eliminate the inter-individual bias inherent in comparing pain measurements between two groups of patients.

**Trial registration:**

ClinicalTrials.gov:
NCT01641718

## Background

### Scientific background and explanation of rationale

Inguinal hernias are the most common hernia; they account for 90% of all spontaneous hernias. Moreover, inguinal hernia repair is the most frequently performed procedure in general surgery. In Germany, more than 200,000 inguinal hernias are repaired annually
[1,2]. The standard method for repairing an inguinal hernia, originally described by Bassini in 1889, is to close the inguinal canal with sutures. Due to the high recurrence rate with this technique
[3], new methods were established that used tension-free implantation of synthetic meshes. Furthermore, endoscopic/laparoscopic methods have been introduced, where the hernia canal is typically approached from the posterior side; this approach is directly opposite to the anterior approach used in the open surgery technique. Which of these approaches and methods yields the better results is strongly debated
[4]. Among the various posterior techniques employing preperitoneal mesh implantation
[2,5-7], the two most widely accepted techniques are the transabdominal preperitoneal patch plastic (TAPP) repair and the total extraperitoneal (TEP) repair
[8,9]. There are many indications for both techniques, but the TAPP repair is particularly recommended for recurrent hernias (after an open preperitoneal patch plastic) and difficult hernias (sliding or incarcerated hernias)
[2,8,10]. The TAPP repair has the advantage that it is easier to perform, can be better standardized, and offers the possibility to perform a diagnostic laparoscopy
[2]. Thus, the type of hernia can be assessed immediately on both sides of the groin, and a bilateral repair can be performed without additional incisions. In general, the TAPP repair is easier to learn than the TEP repair
[2,10,11]. Most randomized studies that compared laparoscopic with open repair found that laparoscopy was associated with less postoperative pain, earlier return to work, higher costs, a longer operating time, a longer learning period, and a higher recurrence and complication rate during the early learning phase
[12-14]. In summary, open, mesh-based, tension-free repair remains the standard procedure; however, in the hands of a well-trained surgeon laparoscopic herniorrhaphy can produce excellent results comparable with those of open repair
[14,15].

Many factors determine whether patients experience postoperative pain, including the type of intervention, the presence of complications, patient age, and individual tolerance. In particular, the type of mesh fixation employed for the hernioplasty has a strong influence on postoperative pain
[16,17]. In a recent review, mesh fixation with glue was compared to mesh fixation with staples for an endoscopic inguinal hernia repair
[18]. For the TAPP repair, two randomized controlled trials
[19,20], one non-randomized trial
[21], and two case series
[22,23] were reviewed. The authors of the review found less postoperative pain and more rapid recovery after glue fixation than after staple fixation, without any significant difference in the recurrence rate. Nevertheless, the authors concluded that, due to the overall poor quality of the currently published data, future well-designed studies are required to demonstrate the superiority of fibrin glue over mechanical stapling for mesh fixation. Thus, well-designed, randomized studies that compare glue and staple fixations for TAPP repair remain warranted. Most previous studies applied only one mesh fixation method for patients with bilateral hernias. Only one study compared glue and staple fixations in single patients with bilateral hernias
[24]; interestingly, that study was not included in the review by Schäfer et al.
[18].

This study protocol describes a two-by-two trial design that will be used to compare the two fixation methods in two groups of randomized patients; one group with unilateral hernias and the other group with bilateral hernias. The latter group will allow a comparison of the two methods in a single patient. This design will eliminate the inter-individual bias that may influence the unilateral hernia group. This study focuses on early postoperative pain, particularly during the first two postoperative days. In many other studies, pain is first measured one month after surgery.

### Aim of the study

The aim of this trial is to investigate early and late postoperative pain after laparoscopic hernia repair with the TAPP technique, using either fibrin glue or staples for mesh fixation.

## Methods/Design

The study was planned according to the updated Consolidated Standards of Reporting Trials (CONSORT) statement. The study design is in compliance with the Declaration of Helsinki, the Guidelines of Good Clinical Practice issued by ICH, and the requirements of Swiss regulatory authorities
[25-27].

### Trial design

This trial is a double blind, randomized, controlled trial with a two-by-two design, conducted at a single institution. The study aims to compare pain after mesh implantation, when fixed either with staples or glue, in a superiority analysis. The CONSORT diagram of the trial is depicted in Figure 
1.

**Figure 1 F1:**
[figure not shown]
Consort diagram of the TISTA trial.

### Eligibility criteria and patient recruitment

Patients scheduled for elective laparoscopic primary inguinal hernia repair at the Department of Surgery, Kantonsspital St. Gallen, will be screened for enrollment in the trial. Informed consent will be obtained, at the latest, on the day before surgery, after ascertaining that the patient meets the eligibility criteria.

Patients that match the following criteria are eligible for inclusion in the clinical trial:

• age, 18 years or older

• male gender

• primary hernia repair (no re-operations for a recurrent hernia)

• no chronic pain

• no acute pain that requires analgesics, other than paracetamol or more than a single dose of non-steroidal anti-inflammatory drug treatment within 48 h before surgery

• no current treatment with psychopharmaceutical drugs

• good compliance can be expected

• no mental incapacity

• no known incompatibility (allergies) with Tisseel compounds

• informed consent

Under the following circumstances, patients will be excluded from the trial:

• hernia is inoperable with TAPP, due to the size, previous abdominal surgery (assuming a damaged peritoneum), or expected adhesions

• repair requires an intra-operative change to another hernia repair technique (e.g. open access methods)

• the patient wishes to stop further trial participation

When the patient refuses further participation after receiving surgery, the patient will receive a safety check-up during a one-month follow-up. Otherwise, the patient will not receive the study treatment and will not require a study-related safety follow-up.

### Study objectives and endpoints

The primary objective of this trial is to show that after TAPP repair for unilateral and bilateral inguinal hernias the acute postoperative pain caused by mesh fixation with tissue glue is less than with staple fixation.

The primary efficacy endpoint of the TISTA trial is pain under physical stress at 24 h after surgery. Pain will be rated by the patient using a numeric rating scale (NRS). The NRS ranges from 0 to 10 in steps of one, with 0 representing no pain at all and 10 the worst imaginable pain. The NRS is comparable to the visual analogue scale (VAS) where the degree of pain is marked on a 10 cm long line. In practical terms, average NRS and VAS scores (in cm) can be considered equivalent. The patient is first asked to rate the pain at rest and then to rate it after physical stress. Physical stress is induced by a 90° bending of the hip joint on the operated side(s). The secondary endpoints of the trial and their definitions are summarized in Table 
1.

**Table 1 T1:** Secondary endpoints and definitions

**Secondary endpoints**	**Definitions**
Pain rated before surgery and at 4, 8, 12, 36, 48 h after surgery	Measured on a numeric rating scale from 0-10 at rest and upon bending the hip joint on the operated side
Operating time	Time, in minutes, from the first skin incision to the application of dressing
Length of hospital stay	Time, in days (with one decimal precision), from start of surgery to hospital release
Postoperative analgesic requirements	Amount (g/day) and type (paracetamol, metamizole, morphine) of analgesic required after surgery, before hospital discharge
Incidence of persistent pain (neuralgia)	Neuralgia defined as:
	• The presence of intermittent hyperesthesia, burning sensation, or jabbing pain in the ipsilateral, inguinal area nerves (genitofemoral nerve, lateral cutaneous femoral nerve, ilioinguinal and iliohypogastric nerve) [20,22,27]
	• Evaluation will be performed 14 days, 1, 3 and 12 months after surgery
	• The degree of pain will measured as described above
Postoperative morbidity	Categorized according to Dindo et al [28], and it includes:
	• Wound infection, defined as infections treated without further surgery and identified by clinical examination without microbiological confirmation
	• Hematoma or seroma formation, identified by clinical examination alone, before discharge from hospital, which does not require radiological confirmation
	• Re-operation, defined as the need for re-operation during the initial hospital stay
	• Bleeding
	• Urinary retention, urinary tract infection
	• Pulmonary infection
	• Any serious deviation from the normal postoperative course
Time to return to normal activities	Time, in days, from hospital discharge to first working day
Relapse	Within 1 year of surgery
Economic impact	Calculated based on the following factors:
	• Cost for glue, staples, and instruments to apply glue or staples
	• If relevant: cost for excess operating time for the “slower” mesh fixation
	• Length of hospital stay (cost/day)
	• Medical leave of absence (converted into a monetary amount based on an average salary)

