## Discussion

This study was designed as a randomized trial with a two-by-two, parallel design. We aimed to compare patients with unilateral hernias that received mesh implants, fixed with either tissue glue or staples and to evaluate patients with bilateral hernias that received mesh implants fixed with tissue glue on one side and staples on the other side. In the latter group, the same patient will rate the pain associated with both methods; these ratings will not be influenced by inter-individual biases present in the unilateral hernia arm. To further reduce biases, both patients and observers (staff evaluating the pain) will be blinded to the assigned treatment.

We expect that mesh implants fixed with tissue glue will be associated with less postoperative pain, shorter hospital stay, and a shorter sick leave after the operation compared to implants fixed with staples. In addition to enhancing patient comfort, the tissue glue fixation will also have an economic impact, by reducing health care costs. Because we can evaluate both inter-individual and intra-individual biases in pain perception, this study will provide important insights for future studies that aim to investigate pain. This study will therefore provide novel information that is currently lacking in the literature.

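### Two of the seven morbidity items in Table 1, hematoma/seroma and re-operation, stop counting at discharge; later events drop out of both items, and in the unilateral comparison the observation time may differ by arm

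*Protocol article*

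**What the plan says.** Under postoperative morbidity, Table 1 (Protocol article, Study objectives and endpoints) lists seven items. Two of them carry a time limit, and in both it is the end of the hospital stay. The first of the two is worded "Hematoma or seroma formation, identified by clinical examination alone, before discharge from hospital, which does not require radiological confirmation". The second, which comes next in the table, uses the admission itself as its limit and is worded "Re-operation, defined as the need for re-operation during the initial hospital stay".

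The other five (wound infection, bleeding, urinary events, pulmonary infection and a catch-all for serious deviations) have no stated limit.

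Length of stay is a secondary endpoint in the same table: "Time, in days (with one decimal precision), from start of surgery to hospital release". The Discussion states the direction the investigators expect: "We expect that mesh implants fixed with tissue glue will be associated with less postoperative pain, shorter hospital stay".

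Contacts after discharge are planned. For neuralgia, "Evaluation will be performed 14 days, 1, 3 and 12 months after surgery". Relapse is assessed "Within 1 year of surgery". The Statistical analysis section compares postoperative morbidity by chi-square.

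**The concern.** There are two separate problems.

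1. **Lost events.** A seroma or hematoma first found at the 14-day or 1-month evaluation, or a return to theatre after discharge, does not meet the definition of its own item. This affects unilateral and bilateral patients and does not depend on any difference in stay.

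2. **Unequal observation.** The window closes at discharge, an event after randomization that the treatment may bring forward. If glue patients go home earlier, they have less time in which one of these events can be counted. A chi-square test on proportions does not correct for that. Glue could show fewer such events partly because it was watched for less time, and the error runs in the direction the investigators expect.

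What is at stake is the reading of two secondary safety components. Events that were never recorded cannot be recovered at the analysis stage.

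**Working it through.** **The plan's own figures.** The plan gives no number for this point. The arm size used below comes from Sample size calculation, which reproduces:

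- Unilateral: two-sample t-test, difference 1, SD 1, two-sided alpha 0.05, power 0.90. n = 22.02, rounded up to 23; 23/0.8 = 28.75, so 29 per arm.
- Bilateral: SD of the difference = sqrt(2 × (1 − 0.2)) = 1.265. n = 18.84, rounded up to 19; 19/0.8 = 23.75, so 24.
- Total: 2 × 29 + 24 = 82, as stated.

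These figures concern pain only and do not depend on the morbidity definitions.

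**Which comparison is exposed to which problem.**

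| Group | Later events lost | Observation time can differ between fixations |
|---|---|---|
| Unilateral (58 patients, compared between patients) | yes | yes, through length of stay |
| Bilateral (24 patients, glue on one side and staples on the other, per Trial interventions) | yes | no, both sides share one discharge |

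**Illustration for the unilateral group.** All inputs here are assumptions: true 30-day risk R = 15% in both arms, exponential onset with median m, discharge at day L.

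Recorded rate = R × F(L)/F(30), with F(t) = 1 − exp(−t × ln2/m).

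For m = 4 days: F(1.5) = 0.2289, F(2.0) = 0.2929, F(2.5) = 0.3516, F(30) = 0.9945.

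| Stay, glue / staples (days) | Recorded, glue | Recorded, staples | Ratio | Missed, glue / staples |
|---|---|---|---|---|
| 1.5 / 2.5 | 3.5% | 5.3% | 0.65 | 77% / 65% |
| 2.0 / 2.5 | 4.4% | 5.3% | 0.83 | 71% / 65% |
| 2.0 / 2.0 | 4.4% | 4.4% | 1.00 | 71% / 71% |

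First row in full: 0.15 × 0.2289/0.9945 = 0.0345; 0.15 × 0.3516/0.9945 = 0.0530; 0.0345/0.0530 = 0.65.

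**What drives the result.** R cancels from the ratio. With stays held at 1.5 and 2.5 days, a median onset of 2 days gives 0.70 and one of 7 days gives 0.63, so onset time matters little. The difference in stay matters much more: halving it from 1 day to 0.5 day, by lengthening the glue stay, moves the ratio from 0.65 to 0.83. The documents give no figure for that difference.

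**In patients.** With 29 per arm, the first row is 29 × 0.0345 = 1.0 against 29 × 0.0530 = 1.5, about half an event. The true expectation under the assumed 15% would be 29 × 0.15 = 4.35 per arm. On these assumptions the lost events outnumber the artificial difference.

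**The case against.** The case for leaving the definitions alone has real content.

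- **Only two items are limited.** A reader might infer that the trial's safety comparison as a whole misses late events. The documents do not support that. Five items have no discharge limit, and a serious late complication or return to theatre may be recorded as "Any serious deviation from the normal postoperative course". Fixation failure that shows as recurrence is followed for 1 year. This stands and sets the scope. It does not put such events back into the two named items, and a late seroma that is not serious would not qualify for the catch-all.
- **Bilateral patients are not exposed to unequal time.** This stands for 24 of the 82 planned patients; they are affected only by the loss of later events.
- **The 0.65 ratio is not an estimate.** A reader might infer that glue will look about a third safer. That needs a one-day difference in stay, which is assumed. Pain is also rated up to 48 h by blinded nurses or physicians, which suggests, without saying so, that many patients stay about two days; a 1.5-day stay would end before that rating. This stands.
- **The counts are small.** No sample size is set for morbidity, and half an event per arm could not support a claim that glue is safer. This stands, and it limits the importance of the bias. It is no reason to keep a rule that discards events.
- **The content of the follow-up visits is not described.** The later contacts are listed under neuralgia only, so the cost of adding an item is partly inferred. However, the eligibility section already uses a one-month safety check-up for patients who refuse further participation after surgery, so one month is a safety horizon the protocol itself recognizes.

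**Conclusion.** The point holds for the hematoma/seroma and re-operation items and no further. That later events go uncounted under these two items follows directly from their definitions, in both groups and whatever the stays turn out to be. Bias toward glue is possible in the unilateral comparison only, and only if stays differ in the expected direction. Its size cannot be computed from the documents: under the assumed 4-day median onset the false ratio runs from 0.65 through 0.83 to 1.00, depending on a difference in stay that the protocol does not quantify. The primary endpoint, its confirmatory analysis and the sample size of 82 are unaffected. This is an inexpensive improvement to two secondary endpoints, not a threat to the trial's main result.

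**What to change.** In Table 1, replace the two discharge-based limits by one fixed window from surgery, the same for every patient. For example, count each hematoma or seroma found, and each re-operation performed, up to and including the scheduled 1-month evaluation. Report in-hospital events separately as description, so that comparison with in-hospital rates elsewhere remains possible. With a common window, observation time no longer depends on discharge. The change concerns what is recorded and counted, not how patients are treated.

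The cost is a change of wording in Table 1 and an added item on the existing 14-day and 1-month follow-up forms. Reported complication rates will be higher than in-hospital rates. Because the article says recruitment is under way, the sponsor should also state how the item will be completed for patients already past their 1-month evaluation.

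### In the unilateral comparison, return to work is timed from hospital discharge, so any difference in length of stay enters this endpoint with the opposite sign

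*Protocol article*

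**What the plan says.** All the definitions are in Table 1 of the protocol article (Study objectives and endpoints).

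- Return to normal activities: "Time, in days, from hospital discharge to first working day".
- Length of hospital stay, a separate secondary endpoint: "Time, in days (with one decimal precision), from start of surgery to hospital release".
- Two morbidity items end at discharge: "Hematoma or seroma formation, identified by clinical examination alone, before discharge from hospital" and "Re-operation, defined as the need for re-operation during the initial hospital stay". The other listed items (wound infection, bleeding, urinary events, pulmonary infection, any serious deviation from the normal course) carry no stated discharge limit.
- Analgesic requirement is given as an amount in g/day, by drug, for "analgesic required after surgery, before hospital discharge".

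The Discussion predicts that glue "will be associated with less postoperative pain, shorter hospital stay, and a shorter sick leave". The Statistical analysis section lists time to return to normal activity among the continuous secondary endpoints to be compared by Mann-Whitney U or Wilcoxon tests, and mentions no allowance for stay. The eligibility criteria require male sex and an age of at least 18; they set no upper age limit and no employment condition.

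**The concern.** Discharge happens after randomization, and the protocol itself expects fixation to move it. A clock that starts there does not start at a comparable moment in the two unilateral arms. The Discussion's hypothesis concerns sick leave following the operation, whereas the endpoint counts only the part that falls after discharge. The two benefits predicted for glue, an earlier discharge and an earlier return to work, therefore work against each other in this variable.

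There is also a mismatch between name and definition. The endpoint is named for normal activities but measured by return to paid work. Retired or unemployed men are eligible and can have no value. Employment status is settled before randomization, so this mainly costs patients and leaves the endpoint undefined for some; it need not favor one arm.

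Hematoma/seroma and re-operation have a related, smaller problem. If stay differs, one arm is watched for longer, and in both arms later events fall outside these two definitions.

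**Working it through.** **Stated sample size, for the arm sizes used below.** The inputs from the Sample size calculation section are a difference of 1, SD 1, two-sided 5%, 90% power, correlation 0.2 and 20% drop-out.

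- Two-sample t-test: power is 0.8997 at 22 per arm and 0.912 at 23, hence 23. Then 23/0.8 = 28.75, rounded up to 29.
- Paired t-test: the SD of the difference is √(2 × (1 − 0.2)) = 1.265. Power is 0.885 at 18 and 0.903 at 19, hence 19. Then 19/0.8 = 23.75, rounded up to 24.
- Total: 2 × 29 + 24 = 82, as stated.

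**Return to work.** Let T be days from surgery to the first working day, L the length of stay, and D the documented endpoint. Then D = T − L, and for glue minus staples ΔD = ΔT − ΔL. This identity needs no outside data.

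Illustration with assumed stays of 3 days (staples) and 2 days (glue), so ΔL = −1:

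| Work resumed, days after surgery (staples / glue) | Documented endpoint (staples / glue) | ΔD | ΔT |
|---|---|---|---|
| 14 / 14 | 11 / 12 | +1 | 0 |
| 14 / 13 | 11 / 11 | 0 | −1 |

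The first row creates a glue disadvantage that does not exist; the second hides a real benefit of one day.

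Next, suppose there is no true difference in T, and D has an assumed SD of 2, 3 or 5 days in each arm. The probability that a two-sided 5% t-test (a stand-in for Mann-Whitney) rejects is:

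| Assumed difference in mean stay | Per arm | SD 2 | SD 3 | SD 5 |
|---|---|---|---|---|
| 0.5 day | 29 | 0.155 | 0.096 | 0.066 |
| 0.5 day | 23 | 0.132 | 0.086 | 0.063 |
| 1 day | 29 | 0.465 | 0.239 | 0.116 |
| 1 day | 23 | 0.382 | 0.198 | 0.102 |

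The distortion matters if stay differs by about a day and return times vary little. It is slight for half a day and a wide spread.

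**Hematoma/seroma.** Assume the same constant hazard in both arms and a cumulative risk r by day 7. The proportion of patients with an event by day L is 1 − (1 − r)^(L/7).

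| Assumed r | 2-day stay | 3-day stay |
|---|---|---|
| 5% | 1.5% | 2.2% |
| 10% | 3.0% | 4.4% |
| 20% | 6.2% | 9.1% |

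Here the arm with the shorter stay looks better, the reverse of the return-to-work shift.

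Stays, SDs and risks are all assumptions. The article gives none of them.

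**The case against.** The best defense is that nothing is lost. Stay is recorded for each patient from the start of surgery, so surgery-to-work time can be rebuilt by adding the two endpoints, and medical leave is also costed under economic impact. If glue does shorten stay, the return-to-work shift goes against glue and would not yield a false claim in its favor. Both statements are true. They show that the repair is cheap, but they do not cure the definition, because the variable named for testing is the one counted from discharge.

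It is also fair to object that the size is unknown, since no stay, variance or expected difference is given. That stands, and the figures above are illustrations only.

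Three stronger readings are tempting but not supported:

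- **That morbidity as a whole is cut off at discharge.** Only hematoma/seroma and re-operation are. Nor are later re-operations necessarily lost to the trial: one might count as a serious deviation from the normal course, and one for recurrence comes under relapse within a year.
- **That g/day until discharge builds in a large spurious analgesic difference.** With invented use of 3, 1 and 0 g on days 1 to 3, averaging gives (3 + 1)/2 = 2.0 g/day for a 2-day stay and (3 + 1 + 0)/3 = 1.33 for a 3-day stay, a ratio of 1.5. But Table 1 does not say that use is averaged over the stay; it may mean the amount on each day, and then this ratio does not arise. The pattern cannot describe paracetamol either, which Postoperative care schedules uniformly.
- **That the whole trial is affected.** In a bilateral patient both fixations share one stay, one discharge and one return to work, so stay cannot differ by fixation. The primary endpoint is timed from surgery.

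**Conclusion.** The point holds for the unilateral comparison of return to normal activities. The clock starts at an event that the protocol expects treatment to change, and a difference in stay enters one for one with the opposite sign. The direction follows from the definitions alone; the size depends on a stay difference that the document does not give, and it is zero if stay is equal. The missing value for men not employed is a separate gap that does not depend on stay.

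The discharge limit on hematoma/seroma and re-operation is a lesser point of the same kind. For analgesics, the text supports only that the observation window can differ between arms; it supports no figure for the effect. These are secondary endpoints, and neither the 24 h pain endpoint nor the 82 patients need to change. The definitions should be corrected, at low urgency relative to anything that touches the primary analysis.

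**What to change.** 1. Count return to normal activities from the day of surgery. For men not employed, use the day on which they resume usual activities. The surgery date is already known, so the first change is wording only; the second needs one question at an existing contact.
2. Count hematoma/seroma and re-operation over the same fixed period after surgery in both arms, for example to the 1-month evaluation. That evaluation is specified in Table 1 only for neuralgia, and hematoma/seroma is identified by clinical examination, so it would have to be checked clinically at that contact. This is a small added burden. The other morbidity items need no change on this ground.
3. Keep the pre-discharge g/day figure for analgesics, and report beside it the use of each reserve drug over a fixed early window such as 0-24 h after surgery. Additional analgesics are already documented, so this is a tabulation. A window that runs only while the patient is in hospital would bring the same dependence back.

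No change to treatment, randomization or sample size follows.
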